## Abstract

**Background:**

Mobile money—a service enabling users to receive, store, and send electronic money using mobile phones—has been widely adopted across low- and middle-income economies to pay for a variety of services, including healthcare. However, evidence on its effects on healthcare access and health outcomes are scarce and the possible implications of using mobile money for financing and payment of maternal healthcare services—which generally require large one-time out-of-pocket payments—have not yet been systematically assessed in low-resource settings. The aim of this study is to determine the impact on health outcomes, cost-effectiveness, feasibility, acceptability, and usefulness of mobile phone-based savings and payment service, the Mobile Maternal Health Wallet (MMHW), for skilled healthcare during pregnancy and delivery among women in Madagascar.

**Methods:**

This is a hybrid effectiveness-implementation type-1 trial, determining the effectiveness of the intervention while evaluating the context of its implementation in Madagascar’s Analamanga region, containing the capital, Antananarivo. Using a stratified cluster randomized design, 61 public-sector primary-care health facilities were randomized within 6 strata to either receive the intervention or not (29 intervention vs. 32 control facilities). The strata were defined by a health facility’s antenatal care visit volume and its capacity to offer facility-based deliveries. The registered pre-specified primary outcomes are (i) delivery at a health facility, (ii) antenatal care visits, and (iii) total healthcare expenditure during pregnancy, delivery, and neonatal period. The registered pre-specified secondary outcomes include additional health outcomes, economic outcomes, and measurements of user experience and satisfaction. Our estimated enrolment number is 4600 women, who completed their pregnancy between July 1, 2020, and December 31, 2021. A series of nested mixed-methods studies will elucidate client and provider perceptions on feasibility, acceptability, and usefulness of the intervention to inform future implementation efforts.

**Discussion:**

A cluster-randomized, hybrid effectiveness-implementation design allows for a robust approach to determine whether the MMHW is a feasible and beneficial intervention in a resource-restricted public healthcare environment. We expect the results of our study to guide future initiatives and health policy decisions related to maternal and neonatal health and universal healthcare coverage through technology in Madagascar and other countries in sub-Saharan Africa.

**Trial registration:**

This trial was registered on March 12, 2021: Deutsches Register Klinischer Studien (German Clinical Trials Register), identifier: DRKS00014928. For World Health Organization Trial Registration Data Set see Additional file 1.

**Supplementary Information:**

The online version contains supplementary material available at 10.1186/s13063-021-05694-8.

## Background

Despite the widespread introduction of user-fee exemption policies to improve access to skilled care during pregnancy and childbirth, out-of-pocket (OOP) payments remain the predominant mode for households in sub-Saharan Africa (SSA) to cater for the costs of healthcare [1]. However, direct costs, including consultations, diagnostic procedures, medicines, and surgery, and indirect costs, such as transportation to a health facility or time off work and associated loss of income, often exceed the available assets and savings of a low-income household [2–6]. Assets such as agricultural land or livestock are usually difficult to convert into cash immediately. In addition, many poor households have no assured regular income or collateral to secure a loan, thus preventing insurance companies and financial institutions from providing their services to these potentially high-risk customers [7]. Therefore, every year 1.5% of the population in SSA are pushed into extreme poverty due to catastrophic health expenditure [8, 9]. To prevent medical impoverishment, households depend on remittances from families and friends, turn to borrowing from formal and informal financial institutions and cut back on non-healthcare expenses such as education and food [1, 2]. Besides, household savings can help to protect from the financial burden of unexpected health expenditure [1, 5]. However, poor households often face the need for unexpected and irregular expenses, which may undercut long-term saving goals [10]. In consequence, expectant mothers from poor households in SSA often do not seek skilled care during pregnancy and childbirth to avoid the risk of being driven deeper into poverty [11]. This is further compounded by the widespread disruption of maternal healthcare services due to the COVID-19 pandemic [12].

Within less than a generation, mobile communication has become ubiquitous. During the last 10 years, mobile phone ownership more than doubled in low- and middle-income countries (LMICs) and quadrupled in SSA [13]. Today, almost 80% of worldwide mobile phone subscriptions come from LMICs with more than 75 subscriptions per 100 people in SSA, whereas, at least until 2025, SSA is expected to achieve the strongest growth of mobile phone penetration among world regions [13, 14]. Alongside this mobile revolution followed payment services, also known as mobile money (MM). MM enables users to receive, save, and send electronic money on a digital platform run by a mobile operator, acting as an alternative to cash. MM can also be used to pay for utility bills or goods and services or to receive bulk payments such as salaries. Using low tech such as unstructured supplementary service data (USSD), MM services can be designed to not require a data connection or smartphone capabilities, thus making them suitable for virtually any mobile handset. Cash can be deposited at agents or retail stores and converted into MM and vice versa [15]. Since 2011, MM increased the overall access to financial services in SSA from 23% in 2011 to 43% in 2017 illustrating the financial inclusion of households with low transaction volumes or limited geographical access which are otherwise underserved by the formal banking system [16]. By late 2019, MM services were available in 95 countries with almost half of all MM users being registered in SSA, accounting for around two thirds of the global MM transaction volume [17]. MM frequently allows users to also enroll in additional financial services, including savings and credit schemes or insurances offered by mobile operators or third-party providers. In addition, MM allows users to perform financial transactions with minimal physical contact, which may be beneficial to curb the transmission of infectious diseases.

Owing to its potential to provide users with rapid access to cash and remittances, electronic savings accounts, and insurance schemes, MM is increasingly being used in the health sector in SSA [17]. MM users have an overall lower risk of catastrophic health expenditure during emergency care and are less likely to reduce non-medical expenses for education or food than non-users [18–22]. Services employing MM in the context of public and private healthcare systems have been launched in several countries in the region, including for (micro)insurance schemes [23–26], loans [27], electronic saving platforms [28, 29], and conditional cash transfers [30]. These services have had mixed results. While the Kenyan National Health Insurance Fund has thrived since the introduction of MM-payable premiums [25], a number of smaller services have been taken off the market due to low demand or active-user conversion rate [24, 28, 31]. Among the multitude of medical conditions, maternal healthcare seems particularly well suited for a savings scheme. Specifically, expenses for maternal healthcare are largely predictable both in their timing and amount. However, the potential benefits and implications of using MM and related services for financing and payment of maternal medical expenses have not yet been systematically assessed.

### Madagascar

In Madagascar, an island nation with a population of 25 million and one of the least developed countries worldwide, financial obstacles are a major cause of limited access to skilled maternal healthcare [32, 33]. Only around half of the pregnant women in Madagascar complete 4 antenatal care (ANC) visits as recommended by the World Health Organization (WHO) and 54% of deliveries take place without qualified personnel [32, 34]. The maternal mortality rate in 2017 was 335 per 100,000 live births and was estimated to be up to 3 times higher in the poorest districts of the country [35, 36]. OOP payments represent 24.7% of total healthcare expenditure and despite national efforts to implement universal health coverage (UHC) using mobile technology, there are currently no MM-based dedicated services for pregnancy-related savings, health insurance, or direct cash transfers available in Madagascar. The risk for impoverishing health expenses during pregnancy is high [37–39]. However, within the last decade, mobile phone subscription rates have increased from less than 3 subscriptions per 100 people in 2005 to 40 per 100 in 2018 [13]. The footsteps of this mobile revolution have followed MM services. As a result, MM accounts have overtaken the number of formal bank accounts in Madagascar in 2015 [16]. In preparation for this trial, we conducted a human-centered, mixed-methods design study in Antananarivo, the capital of the island, to determine the structural, contextual, and experiential characteristics of a mobile phone-based savings and payment service for skilled healthcare during pregnancy and delivery. We demonstrated a high degree of perceived usefulness of MM-based savings and payments for maternal healthcare among key stakeholders and women, in particular among those from low-income households [40, 41].

### Conceptual framework and study objectives

We hypothesize that the implementation of a MM-based payment and savings service for maternal healthcare, the so-called Mobile Maternal Health Wallet (MMHW), will improve access to skilled care during pregnancy and childbirth by reducing financial obstacles. To test this hypothesis, we designed a hybrid effectiveness-implementation type-1 trial, called the Madagascar Mobile MOney for maTernal HEalthcare-Related Spending (4MOTHERS) trial, for evaluation of the MMHW in public-sector health facilities in the Analamanga region of Madagascar. Our trial complements the randomized implementation of the MMHW intervention by a non-governmental organization. The reason for facility randomization was to ensure procedural equality as the implementer’s funding constraints limited the number of facilities allocated to the intervention. The 4MOTHERS trial will adopt a multidisciplinary, cluster-randomized approach complemented by a process oriented mixed-methods evaluation to assess the impact of the intervention on (i) maternal and neonatal health outcomes, (ii) financial outcomes, and (iii) its feasibility, acceptability, and usefulness in the context of its implementation. More generally, the trial will contribute to our understanding of the health system impact of a digital tool for financial inclusion and access to essential healthcare services. In doing so, the trial will add to the scarce evidence on the usefulness of digital tools to achieve UHC. The evidence from this trial is important because it can inform governments in SSA on how to improve access to essential healthcare services, and maternal healthcare in particular, in public-sector healthcare systems.

### Primary and secondary outcomes

Our primary outcomes are (i) woman delivering at a health facility (facility-based delivery), (ii) ANC visits at a health facility per woman (ANC visits), and (iii) total health expenditure during pregnancy, delivery, and neonatal period (total healthcare expenditure).

Our secondary outcomes are as follows:

(i) Maternal and newborn health outcomes include the following:
Pregnancy or childbirth-related diagnoses and complicationsPostpartum depressionMaternal and neonatal mortality

(ii) Economic outcomes include the following:
Remittances received from relatives and friendsRelative household health expenditureImplementer costs and public sector costs of the interventionCost-effectiveness of the intervention for ANC and facility-based deliveryParticipants’ financial distress due to maternal and neonatal healthcare costs

(iii) Measurements of participants’ and healthcare providers’ experience, satisfaction, and behavior include the following:
Time to seek medical attentionMMHW usageUser and health system satisfaction

A complete list of registered and unregistered outcomes for this trial is shown in Table 1.

**Table 1 Tab1:** Primary and secondary outcomes of the 4MOTHERS trial

Outcomes	Definition	Variable/unit	Data source
**Primary outcomes**			
Facility-based delivery^a^	Woman delivering at a health facility	Binary variable	Quantitative household survey
ANC visits^a^	ANC visits at a health facility per woman	Count variable	Quantitative household survey
Total healthcare expenditure^a^	Total health expenditure during pregnancy, delivery and neonatal period per woman	Continuous variable	Quantitative household survey, mmhw dashboard

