#### Restricted cash transfers and electronic vouchers

To incentivize users to save for perinatal medical expenses, each amount credited to the MMHW is topped up with a bonus of 50% of the saved amount. This bonus can only be used to pay for maternal healthcare services; it is not credited to a user’s MM account upon completion of the pregnancy or if a participant chooses to end MMHW membership. In addition, upon sign-up and corresponding to current WHO recommendations, users receive electronic vouchers for free-of-charge (i) ANC drugs such as iron and folic acid supplements; (ii) at least one prenatal ultrasound exam taking place before the 20th week of pregnancy and subsequent follow-up ultrasound exams if medically indicated; and (iii) emergency treatment and referral from a primary-care health facility to a reference hospital in case of a medical emergency during pregnancy or childbirth. Users are informed about their eligibility for conditional cash transfers and electronic vouchers by health workers and automated SMS messages. Users can redeem vouchers for ANC drugs at pharmacies of participating health facilities; ultrasound exams are performed by midwives specialized in prenatal ultrasound at participating health facilities at least once a month, and emergency services can be requested 24/7 by health workers using a Toll-free number. Once a new user has registered for the MMHW and before being eligible to receive restricted cash transfers or electronic vouchers, the account is validated by a facility-based health worker or dedicated MMHW health worker by uploading a photo of the user’s ID card or proof of residence using the MMHW’s web-based interface.

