#### Control group

The control group obtains the usual standard healthcare and receives: (i) no MMHW; (ii) no conditional cash transfers or electronic vouchers for ANC drugs, prenatal ultrasound examinations, or emergency evacuations; and (iii) no quality of care assessments and trainings for facility-based health workers other than routine activities performed by the Ministry of Health. There are no restrictions on concomitant care during pregnancy in the intervention and control group during the trial, and we recommended to follow the standard of care for Madagascar.

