#### Population survey-based impact evaluation

Data collection will be performed after the conclusion of the intervention period on 01/01/2022 (Fig. 2). The population-based survey will be conducted by a team of trained research assistants with experience in qualitative and quantitative research. Research assistants will be trained and supervised by the study team. All questionnaires contain questions in English with Malagasy translations. The survey will be conducted in Malagasy. The primary sampling unit is a census enumeration area (Malagasy: “fokontany”). We will randomly select one census enumeration area from each of the catchment areas of each public-sector primary-care health facility participating in this trial. Within each census enumeration area, we will then select all households and interview all consenting women meeting the eligibility criteria. This sampling scheme is self-weighting [52]. During the interview, the women’s maternal health booklet will be consulted and photographed to reduce recall bias. During the interviews, we will collect data from two sources: (i) the maternal health booklet, which all women utilizing ANC receive, and (ii) women’s self-report. These two data sources will allow us to measure all of our primary outcomes and will contribute to a mechanistic understanding between exposure and outcomes. In particular, we will extract the data on ANC visits from the maternal health booklet and elicit self-reported data on all outcomes, including ANC visits. In addition, the interviews will elicit data on demographic, behavioral, and socioeconomic factors. Total patient expenditure will be calculated from direct costs (medication, diagnostic, operation during pregnancy, delivery and neonatal period, referral costs) and indirect costs (opportunity costs).

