#### MMHW project dashboard and implementer records

Data on the intervention costs will be complemented by data from the MMHW dashboard and implementer records. The MMHW dashboard provides data on direct patient-side healthcare uptake and expenditure as well as on conditional cash transfers and electronic vouchers for users and performance-based payments to CHWs. Data on the direct costs of the intervention—including product development, implementation (i.e., hardware), and operation (i.e., hosting and maintenance), will be taken from the implementer’s records.

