#### Analysis of the randomized controlled trial

Our primary analysis will be an intent-to-treat (ITT) causal effect estimation of our registered pre-specified primary and secondary outcomes. The effect sizes determined in the primary analysis provide an unbiased measure of the real-life policy impact of our intervention. As a secondary analysis, we will also conduct a contamination-adjusted intention-to-treat analysis (CA ITT) using an instrumental variable to adjust for bias [58]. For the CA ITT analysis, we will use the random assignment to intervention vs. control facility catchment area of this trial as an instrumental variable (IV) to measure the effect size that would have been attained without “contamination.” Contamination occurs when women who live in an intervention area do not utilize the MMHW and women who live in a control area utilize the MMHW to receive health care. The treatment in the IV analysis is participants’ actual MMHW registration status. The effect size determined in this secondary analysis provides a measure of the full effect that the intervention would have induced in the absence of intervention utilization (or lack thereof) that did not conform with the intervention status intended by the random assignment of geographical communities. We will regress the primary and secondary outcomes (Table 1) on the random assignment of participants to facility catchment intervention vs. control area. For our binary outcomes, we will use modified Poisson regression analysis [59]; for our count outcomes, we will use negative binomial regression; and for our continuous outcomes, we will use linear regression for effect size estimation.

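### Total healthcare expenditure, a primary outcome, lists a data source that exists only for wallet users, while the survey section says booklet and self-report suffice: the two must be reconciled

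*Protocol article*

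**What the plan says.** Table 1 defines the outcome as "Total health expenditure during pregnancy, delivery and neonatal period per woman" and gives its sources as "Quantitative household survey, mmhw dashboard". The other two primary outcomes list the household survey alone.

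The section on the MMHW dashboard and implementer records describes what that source contains: "The MMHW dashboard provides data on direct patient-side healthcare uptake and expenditure as well as on conditional cash transfers and electronic vouchers for users". The Control group section reads: "The control group obtains the usual standard healthcare and receives: (i) no MMHW". The analysis section foresees some crossover, in that it defines contamination to include the case where "women who live in a control area utilize the MMHW to receive health care".

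The section Population survey-based impact evaluation describes a different basis. It names two sources collected at the interview, the maternal health booklet and the woman's own report, and says that these measure all the primary outcomes. The dashboard is not mentioned there. On the calculation it says: "Total patient expenditure will be calculated from direct costs", and it adds indirect (opportunity) costs.

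On subsidies, the section on restricted cash transfers and vouchers says that "each amount credited to the MMHW is topped up with a bonus of 50% of the saved amount". Table 1 gives implementer contributions, and funds from relatives and friends, their own secondary rows. No sentence says whether bonus or voucher amounts fall inside the primary outcome. The Economic evaluation section uses total healthcare expenditure as the incremental cost.

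**The concern.** Randomisation protects the comparison only if the outcome is measured in the same way in both arms. Read as written, Table 1 gives users an electronic payment log in addition to the interview. Non-users in the intervention arm and nearly all control women have the interview alone. Data collection starts on 1 January 2022 for pregnancies completed from 1 July 2020. Recall therefore reaches back up to 18 months for the delivery at the start of the survey, and further for early pregnancy. The booklet does not obviously fill this gap, because the article names only antenatal visits as data to be extracted from it.

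If the log repairs omissions for users only, the intervention mean rises with no change in spending. Intention-to-treat analysis does not remove this. The planned instrumental-variable analysis divides by the difference in registration, so it would enlarge the artefact. The same quantity feeds the cost term of both cost-effectiveness ratios.

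**Working it through.** **Where the sections stand**

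- Table 1: survey plus dashboard.
- Survey section: booklet plus self-report, said to be enough for all primary outcomes.
- Table 1, relative healthcare expenditure: the numerator is total healthcare expenditure, yet the only source listed is the survey.

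A survey-only version of this quantity is therefore already foreseen, and the source of the primary outcome is stated in two incompatible ways.

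**The plan's benchmark**

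The Power calculation section gives a detectable increase of 1,700 MGA with 2,300 women per group, 80% power and two-sided 5%. No standard deviation is stated, so the figure can be neither reproduced nor refuted. Solving for it:

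SD = 1,700 / [(1.960 + 0.842) × √(2 × DEFF / 2,300)]

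- DEFF = 1 (clustering ignored): SD ≈ 20,578 MGA.
- m = 4,600 / 61 = 75.4 and DEFF = 1 + (75.4 − 1) × 0.05 = 4.72: SD ≈ 9,471 MGA.

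The 1,700 MGA serves below only as the plan's own yardstick.

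**Inputs for the illustration**

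- Uptake 50% (Power calculation).
- Cost base 12 USD, an uncomplicated vaginal delivery (Study setting).
- Conversion 535,603 / 248.42 = 2,156 MGA per USD. This is the only ratio in the document; it is a 2011 PPP ratio and not a market rate. Rates of 3,000 and 4,000 are assumptions added to show a range.
- Share of spending that the survey misses, u: not in the document, so solved for.

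**Source artefact, with no true effect**

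Artefact = uptake × u × cost. Setting this equal to 1,700 MGA gives u = 1,700 / (0.5 × 12 × rate).

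- 2,156: 1,700 / 12,936 = 13.1%
- 3,000: 1,700 / 18,000 = 9.4%
- 4,000: 1,700 / 24,000 = 7.1%

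This supposes that the log recovers everything the survey missed. If only half of users' cost passes through the wallet and only that half is repaired, the first figure doubles: 1,700 / (0.5 × 0.5 × 25,872) = 26.3%.

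With no registration in control areas, the instrumental-variable estimate would carry 1,700 / 0.5 = 3,400 MGA.

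**Payer definition, a separate question**

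The bonus is 0.5 / 1.5 = one third of a topped-up balance. With half of users' cost paid through the wallet, counting or not counting it shifts the arm difference by 0.5 × 0.5 × 25,872 / 3 = 2,156 MGA. That is the same order as the yardstick, before any voucher value.

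**The case against.** The strongest reply is that the survey section already describes symmetric measurement. The same interview is held in every catchment area, self-report is collected on all outcomes, and the dashboard section introduces its data as complementing the intervention costs. No sentence says that dashboard entries replace or top up self-report, and how sources are combined is commonly left to an analysis plan, which is not shown. This stands in part. A reader might infer from Table 1 that unequal ascertainment is planned, and the documents do not go that far. They do state two different source lists for one primary outcome, and that is a conflict rather than an omission.

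The payer is also less open than it may look. The survey section speaks of patient expenditure, Table 1 gives implementer money its own row, and the dashboard section lists patient-side spending separately from transfers and vouchers. A reader might infer that the undefined payer lets measurement alone reverse the effect: a gross +1,700 MGA would become 1,700 − 2,156 = −456 MGA net of the bonus. But counting or excluding subsidy is a choice of estimand. Either version is a valid randomised contrast if it is applied equally in both arms.

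A reader might also extend the dashboard concern to relative expenditure and financial distress. Table 1 sources both from the survey alone, so by their stated source it does not reach them.

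Finally, the sizes rest on an assumed recall loss, wallet share and exchange rate. That is correct, and they are offered only as scale.

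**Conclusion.** The point holds as a conflict over sources with a conditional bias. If Table 1 is followed and dashboard entries supplement self-report for users only, a primary outcome is ascertained by exposure, and the error passes into the cost term of the cost-effectiveness ratios. The separation by arm is near-complete rather than absolute, because some use in control areas is foreseen.

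On the document's own uptake, cost and conversion figures, under-reporting of about 13% would be enough to produce the stated detectable difference. That percentage assumes full repair for users and would be higher with partial wallet use. The 12 USD covers an uncomplicated delivery, not total expenditure. If the survey over-reported instead, the artefact would run the other way. The documents support that this could happen, not that it will.

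The treatment of bonus and vouchers needs one explicit sentence. The wording leans towards excluding them but does not say so.

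**What to change.** Reconcile Table 1 with the survey section before data collection starts:

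1. Derive the primary expenditure outcome from the same household-survey questions in both arms. Use the dashboard only to validate self-report among users, or in a labelled sensitivity analysis.
2. State once, identically for both arms, whether bonus and voucher amounts count. The patient-expenditure wording and the separate implementer row suggest that they do not.
3. If they are excluded, add implementer contributions back into the incremental cost of the cost-effectiveness ratios, so that the subsidy does not drop out of the cost.
4. Opportunity costs may stay in the outcome, as the survey section has it.

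The cost is revised wording in Table 1, the survey section and the Economic evaluation section, with a matching registry update because the outcome is pre-registered. No new data are needed. The small downside is that logged payments are not used to fill gaps in users' recall in the primary analysis.
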